The primary aim of the present study is to investigate the effect of interlimb-coordinated intervention on gait and motor function in patients with stroke at the acute stage. It is hypothesized that acute stroke patients who receive interlimb-coordinated intervention will significantly improve gait and upper-limb motor function. These improvements would be significantly higher than those who receive conventional therapy immediately after the 2 weeks of intervention and at the 3- and 6-month follow-up periods. The secondary aim is to investigate the neural plasticity changes that are induced by interlimb coordinated intervention after 2 weeks of intervention and at the 3- and 6-month follow-up periods. It is also hypothesized that the participants who undergo interlimb-coordinated intervention would have stronger cortical activation at rest and during gait and a shorter neural processing time to initiate a motor task than the participants in the control group immediately after intervention and at the 3- and 6-month follow-up periods. 

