### 2.7. Outcome Measures

#### 2.7.1. Primary Outcome Measure

The primary outcome measure is gait speed, which will be assessed by the 10 m walk test. 

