#### 2.7.2. Secondary Outcome Measure

All outcome measures will be recorded at baseline, post-intervention, and at 3 and 6 months post-intervention. Table 1 presents a brief description of each of the secondary outcome measures that will be recorded at all participating centres. The outcome measures of the 10 m walk test, Fugl–Meyer Assessment, and Action Research Arm Test are the recommended outcome measures by expert consensus from national societies in the United States for body function and activity [39]. The Berg Balance Scale (BBS) was also reported to be a tool that is valid, reliable, and sensitive to change in post-stroke balance impairment assessments despite the potential concern of the ceiling and flooring effect [40]. The timed-up and go test (TUG) was initially developed to identify balance impairment [41] and has been reported as a reliable, valid, and easy-to-administer clinical tool that can be used to assess mobility and balance [42]. Both the BBS [43] and TUG [44] are strong fall predictors. The Instrumental Activities of Daily Living has also been reported as an international gold standard despite its limitations and biases [45].

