### 2.12. Sample Size

Sample size calculation will be based on the primary outcome measures of gait speed. An increase in gait speed of 0.16 m/s has been stated as the minimal clinically significant difference in the first 60 days of stroke occurrence [54] that correlating with a meaningful improvement in disability level post intervention. The study will consider 0.3 m/s for power calculation since other study-reported changes below this value are likely to be measurement errors [55].

The sample size was determined using the sample size calculator G*Power. The calculation model is based on the F test family, the statistical “ANOVA: Repeated measures, between factors” test and the “A priori: Compute required sample size–given alpha power, and the effect size” as the power analysis type. Power calculation was based on a mean difference of 0.3 (mean of group 1 = 0.69; mean of group 2 = 0.39) and the standard deviance of each group of 0.75 with a total sample population of 60. A total of 206 participants (103 in each group) is required to provide 95% power and an effect size of 0.2. Taking a 10% missing rate into consideration, a final sample size of 226 participants (113 in each group) was determined. 

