### 4.2. Data Analysis

All statistical analyses will be performed in IBM SPSS version 21 software (SPSS Inc., Chicago, IL, USA). Descriptive statistics will be conducted to describe the sample population. The demographic characteristics and baseline results for the primary and secondary outcome measures will be analyzed using analysis of variance (ANOVA) or Chi-square test for categorical data. A mixed-effect model analysis will be adopted to compare changes in all of the outcome measures between groups at the completion of the intervention and at the 3- and 6-month follow-ups. The mixed-effect model analysis will include treatment, time, and centre as fixed effects, and the participants will be included as the random effect. Changes in the outcome measures will be adjusted for age, sex, centre, and time. The level of statistical significance will be set at *p* < 0.05. Cohen’s d will be calculated to measure the effect size of the difference for every comparison. The effect size will be interpreted as follows: 0.2—small effect size; 0.5—medium effect size; and 0.8—large effect size. Stratification analysis will be conducted to explore the potential effect difference between centres. There are no planned interim analyses or stopping rules, as the power calculation has accounted for loss to follow-up. In the event of missing data during the follow-up period, the modified intention to treat principle will be followed with the last observation carried forward method. 

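### The plan does not fix which gait-speed contrast carries the primary claim, and the stated 95% power belongs to an averaged test rather than to the three visit-wise comparisons

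*Protocol article*

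**What the plan says.** - **Primary outcome (section 2.7.1):** "The primary outcome measure is gait speed, which will be assessed by the 10 m walk test". No visit is named.
- **Schedule (section 2.7.2):** "All outcome measures will be recorded at baseline, post-intervention, and at 3 and 6 months post-intervention", so there are three post-baseline visits.
- **Primary hypothesis (end of section 1):** "acute stroke patients who receive interlimb-coordinated intervention will significantly improve gait and upper-limb motor function", with superiority over conventional therapy expected "immediately after the 2 weeks of intervention and at the 3- and 6-month follow-up periods".
- **Comparisons (section 4.2):** a mixed model is to "compare changes in all of the outcome measures between groups at the completion of the intervention and at the 3- and 6-month follow-ups". "The level of statistical significance will be set at" p < 0.05, and Cohen's d is to be given for each comparison.
- **Model (section 4.2):** "The mixed-effect model analysis will include treatment, time, and centre as fixed effects", with participant as random effect and adjustment for age, sex, centre and time. A treatment-by-time term is not listed.
- **Sample size (section 2.12):** the G*Power procedure is "ANOVA: Repeated measures, between factors", with means 0.69 and 0.39, SD 0.75 and effect size 0.2. It gives 206 participants (103 per group) for 95% power, raised to 226 (113 per group) for missing data.

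**The concern.** Two sets of statements point to different primary tests. The hypothesis and the comparison sentence describe three visit-wise comparisons. The listed model and the sample-size procedure describe one between-group effect averaged over visits. Nothing in the text says which decides the primary claim, or how three visit results would be combined.

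Two things are at stake. If the visit that counts can be settled once the results are known, the 5% level does not describe the error rate of the primary conclusion. And the 95% power was calculated for the averaged test, so it does not carry over to a test at one visit or to a requirement that all three visits succeed.

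**Working it through.** **Inputs.** From section 2.12: difference 0.3 m/s, SD 0.75, 103 per arm (N = 206), power 95%, effect size f = 0.2. From section 4.2: alpha 0.05, taken as two-sided. The correlation between repeated measurements is not stated, so it is an assumption and is varied.

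**1. Reproducing the plan's figure.** d = 0.3/0.75 = 0.40 and f = d/2 = 0.20. For the named procedure with m measurements and correlation ρ:

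λ = f² · N · m / (1 + (m − 1)ρ), with 1 and N − 2 degrees of freedom.

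With m = 4 and ρ = 0.5, λ = 0.04 × 206 × 4 / 2.5 = 13.18 and power is 0.951. N = 206 is the smallest even total that reaches 95%. At ρ = 0.5 the other choices of m need 220 (m = 3), 246 (m = 2) and 328 (m = 1). At m = 4, ρ = 0.3 needs 158 and ρ = 0.7 needs 254. The plan's N is thus reproduced as an averaged group effect over four measurements, with an assumed correlation of 0.5.

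**2. The averaged effect over the three post-baseline visits only.** With m = 3, ρ = 0.5 and N = 206, λ = 0.04 × 206 × 3 / 2 = 12.36 and power is 93.8%. At ρ = 0.7 it is 89.1%.

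**3. One visit.** The mean z is 0.40 × √(103/2) = 2.87. The noncentral t gives power 81.5% with 103 per arm and 84.9% with 113. Reaching 95% at one visit needs about 163 to 164 evaluable per arm.

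**4. Any of three visits, no true effect.** The risk is P(at least one |z| > 1.96) for three equally correlated normal statistics.

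| Correlation between tests | Two-sided risk | Errors favouring the intervention only |
|---|---|---|
| 0 | 14.3% | 7.3% |
| 0.5 | 12.5% | 6.3% |
| 0.7 | 10.9% | 5.5% |
| 0.9 | 8.4% | 4.2% |

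The reference values for a single test are 5% and 2.5%. A correlation of 0.5 is a natural case. If all visits are equally correlated at ρ, two change scores sharing a baseline correlate at (1 − ρ)/(2(1 − ρ)) = 0.5, whatever ρ is.

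**5. All three visits significant, 0.3 m/s at each.** With SD held at 0.75 and 103 per arm, power is 54.9% at correlation 0, 64.1% at 0.5, 68.5% at 0.7 and 74.5% at 0.9. With 113 per arm and correlation 0.5 it is 69.6%.

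Holding the SD fixed is not the only reading. On change scores the SD is 0.75 × √(2(1 − ρ)). With baseline as covariate it is 0.75 × √(1 − ρ²), and the tests correlate at (ρ − ρ²)/(1 − ρ²).

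| Raw correlation ρ | Change scores | Baseline as covariate |
|---|---|---|
| 0.5 | 64% | 79% |
| 0.6 | 77% | 87% |
| 0.7 | 90% | 95% |

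The adjustment list in section 4.2 does not include baseline gait speed.

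**The case against.** The best defence is that the plan already contains one primary test. Without a treatment-by-time term, the listed model yields a single treatment effect, tested once at 5%, and section 2.12 powers that kind of test. This reading is legitimate, and it means three separate primary tests cannot be asserted as settled. It does not close the matter. The sentence just before the model asks for comparisons at each of three times, and the hypothesis expects superiority at each.

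A reader might infer that success at any one visit counts, and so that the trial runs a 12.5% error rate. The documents do not say so. The hypothesis joins the visits with *and*, and no decision rule is given. The any-of-three figures apply only if that rule were adopted, and they are roughly halved when only errors favouring the intervention count. Equally, no text makes success at all three visits a requirement, so 64% is not the trial's power. It lies toward the low end of a range that depends on an unstated correlation and on the analysis used.

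A reader might also infer that upper-limb measures are co-primary. The abstract and Table 1 list them as secondary. What remains is a wording tension with the primary aim.

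Finally, detailed multiplicity procedures may sit in an analysis plan that is not shown, and their absence from an article is no fault. The point here rests on statements in the article that do not agree with each other.

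**Conclusion.** The concern holds in a limited form: the primary gait-speed contrast is not fixed, and the 95% power does not belong to the visit-wise comparisons that the text describes. Power is 81.5% for one visit on the stated inputs without baseline adjustment. For all three visits it runs from about 64% to 90% on change scores (raw correlation 0.5 to 0.7), and from 79% to 95% with baseline adjustment. Under an any-one-visit rule the two-sided error risk would be 8.4% to 14.3% for correlations from 0.9 down to 0.

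These figures assume SD 0.75 and an equal 0.3 m/s effect at every visit, normal test statistics and equal correlations. The mismatch between the sections does not depend on any of these assumptions.

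**What to change.** Name one primary gait-speed contrast, tested at two-sided 0.05. There are two sound options:

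- **(a)** the treatment effect averaged over the post-baseline visits, which fits the sample-size procedure;
- **(b)** the treatment effect at one named visit, with treatment-by-time added to the model.

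Treat the other visit-wise gait comparisons as secondary, or test them in a fixed order, each only if the one before is significant. Reword the primary aim so that upper-limb function matches its secondary status.

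Restate the power for the chosen contrast. On the stated inputs, option (b) has about 82% with 103 per arm and about 85% with 113, without baseline adjustment. Option (a) has about 94% with 206 participants at an assumed correlation of 0.5, since the plan's N is reproduced with four measurements rather than three.

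The change is to wording and to the power statement. The cost is that the stated power may look less favourable, and that the other visits lose confirmatory status if the primary test fails.

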## 5. Discussion

Several clinical guidelines propose that active rehabilitation is to be provided within 24–48 h of stroke occurrence [57], as the most considerable amount of the recovery was reported to take place in the first month following stroke [58]. Available evidence supports the benefits of early rehabilitation intervention on motor recovery, but convincing evidence for an early interlimb coordinated intervention is lacking. Thus, this study will provide evidence on the feasibility and efficacy of interlimb coordinated movement as part of an early intervention program for gait and motor function improvement. The medium long-term efficacy of the interlimb coordinated intervention will also be assessed in this study. Several Cochrane reviews regarding the efficacy of other interventions on motor function recovery seldom report data beyond the initial discharge period [59] or has followed up beyond the three [60] or six month periods [61]. As motor function capacities evolve the most during the first month of stroke onset [62], it is anticipated that intervention provided during the acute stage of stroke has better clinical outcomes when compared to interventions that are provided at later stroke stages. Therefore, 3- and 6-month post-intervention follow-up data will increase the understanding of whether interlimb coordinated intervention is superior to conventional therapy in the longer term. 

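### Last observation carried forward is the stated method for missing follow-up, although the planned mixed model does not need it and its flat-course assumption conflicts with the protocol's own account of early recovery

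*Protocol article*

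**What the plan says.** Section 4.2 (Data Analysis) sets out the main analysis: "A mixed-effect model analysis will be adopted to compare changes in all of the outcome measures between groups" at the end of treatment and at 3 and 6 months. The model "will include treatment, time, and centre as fixed effects, and the participants will be included as the random effect".

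The same section then fixes the handling of missing follow-up values: "the modified intention to treat principle will be followed with the last observation carried forward method". No other method for missing data is stated.

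Four other places bear on the point:

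- Section 2.4 admits patients with a first stroke within the preceding month.
- Section 5 (Discussion) says that "the most considerable amount of the recovery was reported to take place in the first month following stroke".
- Section 1 hypothesises superiority straight after the 2 weeks of treatment and again at 3 and 6 months.
- Section 2.12 allows for 10% missing data, with no split by arm.

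**The concern.** Last observation carried forward (LOCF) gives a patient who is lost after the 2-week visit that same gait speed at 3 and 6 months. This is right only if the patient stops changing at the last visit. The article describes a population that is still recovering, so a flat profile is at odds with its own clinical picture.

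The rule also works against the planned model. A likelihood-based mixed model with a participant effect uses whatever visits each patient has, and is valid if data are missing at random. Once every follow-up gap is filled, the model has no gaps left to handle and treats each filled value as a measurement.

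The 3- and 6-month comparisons named in the hypothesis are at stake. If dropout differs between arms, LOCF turns part of that difference into a difference in gait speed. If dropout is equal but the treatment effect is still growing, LOCF shrinks it.

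**Working it through.** **The plan's own figure.** Inputs from section 2.12: means 0.69 and 0.39 m/s, SD 0.75, effect size 0.2, power 95%. The four visits come from section 2.7.2. The between-visit correlation of 0.5 is an assumption, because the article does not give it.

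- f = (0.30/2)/0.75 = 0.20.
- Noncentrality = N·f²·m/(1+(m−1)ρ) = 206 × 0.04 × 4/(1 + 3 × 0.5) = 13.18, with 1 and 204 degrees of freedom. Power is 0.951, so 206 reproduces.
- 206 × 1.10 = 226.6, reported as 226.

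Nothing in this calculation depends on LOCF.

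**Bias formula.** Let d be the dropout proportion in an arm and r the mean recovery from the last observed visit to 6 months, with dropouts otherwise like completers. The LOCF mean of an arm is its true 6-month mean minus d·r. Therefore:

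bias in (intervention − control) = d_C·r_C − d_I·r_I

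**No true effect, same recovery in both arms.** Bias = (d_C − d_I)·r. The dropout splits and r are assumptions.

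| Dropout control:intervention | r = 0.2 m/s | r = 0.3 m/s |
|---|---|---|
| 10:10 | 0 | 0 |
| 15:5 | 0.10 × 0.2 = 0.02 | 0.10 × 0.3 = 0.03 |
| 20:5 | 0.15 × 0.2 = 0.03 | 0.15 × 0.3 = 0.045 |
| 5:15 | −0.02 | −0.03 |

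Against the 0.16 m/s minimal difference in section 2.12, 0.03 is 0.03/0.16 = 19% and 0.045 is 28%.

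**Type I error.** Simulation with 113 per arm, correlation 0.5, loss after week 2, and analysis of covariance on the 6-month value:

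| Dropout | r | SD 0.75 (protocol) | SD 0.40 (assumed) |
|---|---|---|---|
| 15:5 | 0.2 | 5.0% | 7.2% |
| 15:5 | 0.3 | 6.6% | 9.6% |
| 20:5 | 0.2 | 6.7% | 8.7% |
| 20:5 | 0.3 | 8.2% | 14.8% |

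The runs numbered 5000 per case at SD 0.75 and 4000 at SD 0.40. A second set of 4000 runs gave 5.7-8.3% and 6.7-15.1% over the same four cases. The Monte Carlo standard error near 5% is √(0.05 × 0.95/5000) = 0.3 points. Analysis of the observed values alone stayed close to 5%.

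**Equal 10% dropout, true 6-month effect.** Bias = −0.10 × (part of the effect that arises after the last visit).

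- Effect 0.16, none of it present at week 2: 0.16 − 0.016 = 0.144. At SD 0.40, power falls from 90-91% to 83-85%.
- Effect 0.16, half present at week 2: 0.16 − 0.008 = 0.152.
- Effect 0.16, all present at week 2: 0.16, with no loss of power.
- Effect 0.30 at SD 0.75, none present at week 2: 0.27. Power falls from roughly 91% to roughly 87%.

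**If a baseline value is carried.** Take mean speeds rising from 0.30 to 0.55 (control) and from 0.30 to 0.85 (intervention), with dropout 5:15. The bias is 0.05 × 0.25 − 0.15 × 0.55 = −0.07, so a true 0.30 becomes 0.23. This was the largest bias among the scenarios tried.

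**Precision.** In one null scenario (10% dropout in both arms, SD 0.75, 150 simulated trials with a participant random effect), the mean model standard error was 0.0997 with LOCF and 0.1033 on observed data. The ratio is 0.965, or about 3.5% smaller.

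**The case against.** Much of the case on the other side stands.

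- **Size.** The larger type I errors need an SD of 0.40. The protocol's own SD is 0.75, and there the excess is small.
- **Dropout imbalance.** Nothing in the article predicts it. Therapy time is equal in both arms (section 3.2, Table 3) and follow-up travel is reimbursed (section 2.6). The 20:5 split averages 12.5%, above the planned 10%.
- **Power loss.** The drop from about 91% to about 84% requires no effect at week 2. Section 1 hypothesises an effect at that time, and with the full effect already present nothing is lost.
- **Recovery after week 2.** The article gives no such figure. The 0.33 and 0.65 m/s in section 1 come from separate populations. Since entry may be up to a month after stroke, the post-treatment visit can fall after the steepest recovery.
- **Simulation model.** It used analysis of covariance at one visit, not the planned repeated-measures model, and dropout was unrelated to outcome.

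A reader might also infer several stronger things that the documents do not support:

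- That LOCF does nothing but add bias. With equal dropout and parallel later recovery it adds none.
- That the trial is open-label. Section 2.1 says single-blinded and section 2.11 blinds the assessors, although participants can hardly be unaware of the ergometer.
- That patients lost before week 2 are certainly assigned zero change. Section 1 uses the follow-up term for 3 and 6 months, so the rule's reach back to week 2 is unclear.
- That the text makes LOCF override the model. The order of steps is not stated; this follows only because no gaps remain once they are filled.
- That patients who later lose walking ability count against LOCF alone. A missing-at-random model mispredicts them too.

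None of this supplies a reason to prefer LOCF. Its bias depends on dropout and recovery patterns that nobody knows in advance, so it cannot be defended as conservative.

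**Conclusion.** The point holds in a moderate form. LOCF is a stated choice, not a detail left to the statistical analysis plan. It rests on a flat course that the article's own account of recovery contradicts, and it sits beside a model that does not need it.

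The harm falls mainly on the 3- and 6-month comparisons; the 2-week comparison is largely untouched. At the planned 10% overall missingness the bias was 0 to 0.03 m/s in most scenarios, against a minimal difference of 0.16 m/s. It reaches 0.045 m/s with 20:5 dropout. Its direction follows the dropout imbalance and the timing of the effect. The type I error of about 6-8% applies to the protocol's SD of 0.75; the range of about 7-15% applies only if the true SD is nearer 0.40. Dropout splits, later recovery and the correlation of 0.5 are all assumptions.

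**What to change.** In section 4.2, delete LOCF as the main method. State that the planned mixed model will be fitted by likelihood to all observed values of all randomised participants, analysed as allocated, under missing-at-random. Except from this the data of participants who withdraw completely, which section 2.6 removes from the study, and make the population label agree with that description. LOCF, if kept at all, should be a labelled sensitivity analysis.

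A sensitivity analysis for departures from missing-at-random would be a useful addition but may be left to the statistical analysis plan.

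The cost is analysis wording only. No further patients or data are needed, and 206/226 is unchanged. The change should be made before any unblinded outcome data are seen, so that it cannot look data-driven.

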## 5. Discussion

Several clinical guidelines propose that active rehabilitation is to be provided within 24–48 h of stroke occurrence [57], as the most considerable amount of the recovery was reported to take place in the first month following stroke [58]. Available evidence supports the benefits of early rehabilitation intervention on motor recovery, but convincing evidence for an early interlimb coordinated intervention is lacking. Thus, this study will provide evidence on the feasibility and efficacy of interlimb coordinated movement as part of an early intervention program for gait and motor function improvement. The medium long-term efficacy of the interlimb coordinated intervention will also be assessed in this study. Several Cochrane reviews regarding the efficacy of other interventions on motor function recovery seldom report data beyond the initial discharge period [59] or has followed up beyond the three [60] or six month periods [61]. As motor function capacities evolve the most during the first month of stroke onset [62], it is anticipated that intervention provided during the acute stage of stroke has better clinical outcomes when compared to interventions that are provided at later stroke stages. Therefore, 3- and 6-month post-intervention follow-up data will increase the understanding of whether interlimb coordinated intervention is superior to conventional therapy in the longer term. 

The key principle of motor function recovery post stroke is neural plasticity. A previous study indicated that function improvement is related to cortical reorganization post-intervention [53]. However, the optimal strategy for intervention application in order to increase cortical activation and motor skill learning has yet to be determined [27]. Early literature indicated that the activation patterns related to bimanual task performance were not similar to unimanual tasks such as finger opposition [63]. Recent literature propagates the theory that unimanual motor tasks involve bi-hemispheric activation patterns that are similar to the bilateral neural activation that is typically observed during bimanual movements [64]. This theory is given further support by a study that reported bimanual coupling effects observed during affected and unaffected hand tasks in an individual with stroke [65]. Another study utilized fMRI to compare the inter-regional connectivity and inter-regional activation between the bimanual in-phase and bimanual antiphase upper limb task in healthy individuals. Significant activation of the supplementary motor area, cerebellum, thalamus, and the cingulate motor area were observed during the bimanual antiphase task but not during in-phase movement [66]. The connectivity analysis also indicated stronger neural coupling during antiphase movement than during bilateral in phase and unimanual movement. Antiphase movement is similar to gait and requires the precise spatial and temporal control of the limbs. Spatial and temporal control is also required during single-hand movement due to the inhibition of the ipsilateral motor area, as evidenced by the presence of neural activity in the bilateral motor cortex [67]. It is anticipated that the interlimb-coordinated intervention that is provided at the acute stage will provide higher inter-regional connectivity and cortical activation when compared to conventional therapy, providing further evidence to support the regime to improve motor function in patients with stroke. In conclusion, this proposed research is set to provide information on the interlimb coordinated intervention as an early intervention program for patients with stroke. 

